### Data management

The data dictionary for ICEAGE is supplied in Additional file 6. Data will be collected from participants using a standardised electronic case report form (CRF) and stored in participating centres’ password protected electronic hard drives. To ensure correct data entry, the CRF has been designed with extensive use of data entry limitation rules and on-screen prompts. Site investigators will be required to perform random covert audits of data collected by trial personnel during the trial for reliability and correctness against the medical record. There are no industrial contractual arrangements in relation to the de-identified data. On completion of the trial, the database will be made available for independent analysis or as an appendix in the publishing journal if requested.

### Statistical analysis

#### Sample size

PPC rates previously reported following emergency abdominal surgery are between 30 and 40% [3, 4, 27]. A 2013 prospective audit (unpublished) of PPC incidence in 50 consecutive patients at the primary participating centre found a rate of 20% (95%CI 10–34%). A 60% relative risk reduction in PPC with timely physiotherapy can be achieved in the elective abdominal surgery population [16]. A total sample size of 262 completed participants (131 per group) is required to detect a reduction in PPC rate by 60% from an anticipated baseline of 20% (20% down to 8%) with an alpha 0.05 and power 80%. This is arbitrarily increased to compensate for a possible 10% drop out/withdrawal rate and uncertainty around baseline incidence and effect size. In total, a sample of 288 participants is required for this trial.

#### Statistical methods

Imbalances of potential confounding variables between trial groups at recruitment will be assessed. Adjustment covariates will be selected by backward stepwise regression from covariates that are anticipated to affect incidence of PPC. These include respiratory comorbidity, smoking history, age, gender, length of operation, operation category (upper gastrointestinal, colorectal, urological, other), and ICU admission immediately following the procedure.

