##### Primary outcome

The absolute and relative rates of PPC in the trial groups will be estimated using multivariate robust random effects Poisson generalised linear regression to allow assessment of binary outcomes with or without adjustment for potential confounding variables (incidence rates and rate ratios, 95% confidence intervals, *p* values). Treatment centre will be treated as a fixed variable in multi-level models. In addition, the effect of time from the end of surgery/anaesthesia to commencement of symptoms of PPC will be compared using Cox proportional hazards regression with and without covariate adjustment (hazards ratio, 95% confidence intervals, *p* values). A Kaplan-Meier graphic representation of this analysis will be performed.

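### The adjustment covariates are to be picked by stepwise selection on the trial's own data, and the plan does not say whether the adjusted or the unadjusted PPC rate ratio decides the trial

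*Protocol article*

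**What the plan says.** Under Statistical methods, the article first says "Imbalances of potential confounding variables between trial groups at recruitment will be assessed". It then gives the selection rule: "Adjustment covariates will be selected by backward stepwise regression from covariates that are anticipated to affect incidence of PPC". The candidates follow: "These include respiratory comorbidity, smoking history, age, gender, length of operation, operation category (upper gastrointestinal, colorectal, urological, other), and ICU admission" straight after the procedure. The opening words leave the list open. No removal threshold is given, and the text does not say that treatment is kept in the model throughout.

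Under Primary outcome, absolute and relative PPC rates come from a robust random effects Poisson regression, "with or without adjustment for potential confounding variables", with centre as a fixed variable. A Cox analysis of time to PPC, both adjusted and unadjusted, is then introduced as an additional analysis.

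Under Sample size, the trial is sized on one comparison of two proportions (20% against 8%, alpha 0.05, power 80%): "A total sample size of 262 completed participants (131 per group) is required".

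Under Blinding, data analysts and statisticians are blinded to allocation.

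**The concern.** In a randomised trial, covariates earn their place by being prognostic, and they can be fixed before any outcome is seen. Here the adjusted model is built from the outcome data it will then be used to test. Its reported standard error treats the final covariate set as if it had been given in advance. With few events, the chosen set is also likely to be unstable.

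The larger issue is that the sample size spends one alpha of 0.05 on one comparison, while the analysis section supplies two Poisson rate ratios, each with a p value. If they fall on opposite sides of 0.05, the protocol does not say whether the trial is positive.

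**Working it through.** **1. The plan's own figure.** Inputs from Sample size: p1 = 0.20, p2 = 0.08, alpha 0.05 (taken as two-sided), power 80%. With mean rate 0.14, n per arm = [1.960 × √(2 × 0.14 × 0.86) + 0.842 × √(0.20 × 0.80 + 0.08 × 0.92)]² / 0.12² = (0.9618 + 0.4068)² / 0.0144 = 130.1, rounded up to 131. That is 262 in total, as stated, and 262 × 1.10 = 288.2 matches the 288. The size thus rests on a single unadjusted comparison of proportions.

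**2. Expected events.** With 288 analysed: 144 × (0.20 + 0.08) = 40.3. With 10% lost: 129.6 × 0.28 = 36.3.

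**3. Terms in the starting model.** Six covariates at one coefficient each (assuming binary smoking history and linear age) plus three for the four-level operation category make 9. Adding treatment and two centre terms makes 12, not counting the intercept. Events per term: 36.3/12 = 3.0 to 40.3/12 = 3.4. If the control rate were instead the 30 to 40% that Sample size also cites, with the same 60% reduction, events would be 144 × 0.42 = 60.5 to 144 × 0.56 = 80.6, or 5.0 to 6.7 per term.

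**4. Type I error.** I simulated trials with no treatment effect: n = 288, 6,000 trials per scenario, robust Poisson with fixed centre terms in every model, treatment forced in, and backward elimination with operation category tested as a block. The Monte Carlo standard error is √(0.05 × 0.95/6000), about 0.3 points. The documents give no covariate effects, so these are assumptions. The moderate setting used log-odds of 0.6 for respiratory comorbidity and for ICU admission, 0.4 for smoking, 0.25 per SD for age and for operation length, 0.15 for gender, and up to 0.5 for operation category. The strong setting doubled them. Rejection at nominal 5%, in per cent:

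| PPC rate | Covariates | Removal p | Unadjusted | All seven fixed | Stepwise | Unadjusted or stepwise | The two disagree |
|---|---|---|---|---|---|---|---|
| 20% | none | 0.05 | 4.98 | 5.00 | 4.97 | 5.27 | 0.59 |
| 14% | moderate | 0.05 | 4.25 | 4.63 | 5.03 | 5.60 | 1.92 |
| 20% | moderate | 0.05 | 4.57 | 5.30 | 5.10 | 6.15 | 2.63 |
| 20% | moderate | 0.20 | 4.52 | 5.22 | 5.72 | 6.58 | 2.92 |
| 35% | moderate | 0.05 | 4.87 | 5.23 | 5.38 | 6.63 | 3.01 |
| 35% | strong | 0.05 | 4.58 | 5.43 | 5.57 | 7.62 | 5.09 |
| 20% | strong | 0.05 | 4.88 | 5.20 | 5.70 | 7.67 | 4.76 |

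The last column is 2 × (either rejects) − unadjusted − stepwise; for example 2 × 6.15 − 4.57 − 5.10 = 2.63.

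**5. Reading the table.** A single model fixed in advance holds its level: 4.3 to 5.0% unadjusted, 4.6 to 5.4% with all seven covariates. Stepwise alone gives 5.0 to 5.7%. Taking whichever of the unadjusted and stepwise results is significant gives 5.3 to 7.7%. Two independent tests would give 1 − 0.95² = 9.75%, but these two are highly correlated, so the figure is well below that. With no true effect, the two analyses disagree at the 5% level in about 0.6 to 5.1% of trials.

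**The case against.** **The error rate.** A reader might infer that the error rate simply exceeds 5%. The documents do not support that. The protocol nowhere plans to report the better of two results, and each analysis taken alone is close to nominal. Clear inflation needs a favourable choice, and its size rests on assumed covariate effects. This objection stands.

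**The number of candidates.** It is also tempting to count four primary answers, adding the two Cox results. The text points the other way. Cox is brought in as an addition, Secondary outcomes lists PPC among the time-to-event outcomes, and the sample size is for two proportions. Two results compete, not four.

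**Imbalance.** A reader might infer that covariates will be chosen because of chance imbalance. The article says only that imbalance will be assessed and links no adjustment to it. The candidate pool is defined by expected prognosis, and seven members are named.

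**Blinding.** Analysts blinded to allocation have less scope for deliberate choice. That is a real safeguard, but it does not say which estimate decides.

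**Sparse data.** More events would ease the problem, and a fixed list does not remove it. Age, respiratory comorbidity, smoking, ICU admission and a three-level operation category take 6 coefficients. With treatment and centre that is 9 terms, or 36.3/9 = 4.0 to 40.3/9 = 4.5 events per term. The gain lies in removing the data-driven choice more than in relieving sparsity.

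**A separate analysis plan.** One may exist and may name the primary estimate. Mere silence on that would carry little weight. But the stepwise rule is stated here, and a later plan could mend it only by departing from this text.

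**Conclusion.** The point holds as a defect in a rule that the article does state. Covariates are selected on the trial's own outcome data from an open-ended list, and neither of the two Poisson rate ratios is designated as deciding. The main reason to act is the undefined deciding result; the numerical inflation is secondary. Selection alone adds at most about 0.7 points to the 5% level, and choosing the favourable version adds about 0.3 to 2.7 points. These sizes depend on the assumed covariate prevalences and effects, on treatment being forced into the model, and on removal thresholds of 0.05 or 0.20, none of which the article gives. The event counts depend on the design rates of 20% and 8%. No claim is made that the planned analysis as such runs above 5%.

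**What to change.** Delete the stepwise selection. Name one primary estimate: the robust Poisson rate ratio adjusted for centre and a fixed short list taken from the covariates already named. An example is age, respiratory comorbidity, smoking history, ICU admission straight after surgery, and operation category with the urological level merged into other, as the sensitivity analyses already group it. State that this list applies whatever imbalance is observed. Label the unadjusted Poisson result as supportive, and say explicitly that the Cox analyses are supportive too, which the text already implies.

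The cost is one paragraph. Patients are recruited from the ICU and wards and randomised within 48 h of surgery, so these covariates are essentially settled before allocation. The 262 and 288 stand. The small downside is that some of the fixed covariates may prove only weakly prognostic.

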##### Primary outcome

The absolute and relative rates of PPC in the trial groups will be estimated using multivariate robust random effects Poisson generalised linear regression to allow assessment of binary outcomes with or without adjustment for potential confounding variables (incidence rates and rate ratios, 95% confidence intervals, *p* values). Treatment centre will be treated as a fixed variable in multi-level models. In addition, the effect of time from the end of surgery/anaesthesia to commencement of symptoms of PPC will be compared using Cox proportional hazards regression with and without covariate adjustment (hazards ratio, 95% confidence intervals, *p* values). A Kaplan-Meier graphic representation of this analysis will be performed.

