### Trial design

ICEAGE is a pragmatic, multicentre, parallel-group, randomised controlled trial. It is patient and assessor blinded, and powered for superiority. Eligible patients will be randomly assigned via concealed allocation into one of two physiotherapy treatment arms (Table 1). The control group will receive standard care physiotherapy from the first postoperative day consisting of education on prevention of complications with upright positioning, ambulation, and breathing exercises; a single deep breathing and coughing (DB&C) coaching session; and no more than 15 min of supervised ambulation once daily until a threshold score is met to discharge from this service. The intervention group will receive an enhanced physiotherapy care package from the first postoperative day consisting of (i) education on prevention of complications with upright positioning, ambulation, and breathing exercises; (ii) at least twice daily coached DB&C for the first two postoperative days; and (iii) at least 30 min of supervised early rehabilitation daily for the first five postoperative days. The mode of ambulation and respiratory physiotherapy will be standardised for both groups. The difference between groups will be (1) additional reminders and education as necessary for performance of independent exercises, (2) longer duration of ambulation and/or provision of individualised rehabilitation exercises, and (3) increased number of coached DB&C sessions (see Fig. 1 for the ICEAGE trial CONSORT diagram).

**Table 1 Tab1:** TIDieR descriptions of ICEAGE interventions

TIDieR criterion	Control	Intervention
Item 1. Brief name: provide the name or a phrase that describes the intervention	Standard care: ‘talk, walk, breathe’	Enhanced physiotherapy care: ‘talk more, exercise more, breathe more’

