### Trial setting

The three participating centres represent a range of hospital types in Australia. The Launceston General Hospital (Launceston, Tasmania, Australia) is a regional primary referral hospital; the Princess Alexandra Hospital (Brisbane, Queensland, Australia), a metropolitan primary referral hospital; and Northeast Health Wangaratta (Wangaratta, Victoria, Australia), a sub-regional secondary referral hospital, are all government-funded, university-affiliated, teaching hospitals.

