### Outcome measures

#### Primary outcome

The primary outcome is the first occurrence of a PPC within the first 14 postoperative hospital days. PPCs will be defined by the Melbourne Group Score (Table 3) which is reliable, valid [27, 28], sensitive to interventions [16], and has high inter-rater reliability [29]. It has eight clinical criteria: four factors relating to symptoms and four to diagnostic markers. A PPC will be diagnosed when four or more factors are present at any time from midnight to midnight on one postoperative day. The day a PPC is first diagnosed is the day of onset for purposes of time-to-event analysis.

**Table 3 Tab3:** PPC diagnostic criteria—Melbourne Group Score Version 3

When four or more of the following criteria^*^ are present anytime in the 24-h period 00:01 to 24:00 on a single postoperative day: 1. New abnormal breath sounds on auscultation different to preoperative assessment^+^ 2. Production of yellow, green, or brown sputum different to pre-morbid status^+^ 3. Pulse oximetry oxygen saturation (Sp0_2_) < 90% on room air or FiO2 on 0.21 on more than one consecutive postoperative day^**^ 4. Raised maximum tympanic temperature ≥ 38 °C on more than one consecutive postoperative day 5. Chest radiograph report of collapse/consolidation^# ***^ 6. Presence of infective organisms on sputum culture report^***^ 7. White cell count > 11 or < 3 8. Physician’s diagnosis of postoperative pulmonary complication (e.g. atelectasis, pneumonia, AECOPD, respiratory failure, upper respiratory tract infection) OR prescription of an antibiotic specific for respiratory infection	

*Abbreviations*: *PPC* postoperative pulmonary complications, *SpO2* pulse oximetry, *FiO2* fraction of inspired oxygen, *AECOPD* acute exacerbation of chronic obstructive pulmonary disease, *PEEP* positive end expiratory pressure, *CXR* chest X-ray

*If a blinded physiotherapist, nurse, or physician documents in the medical record the occurrence of a criterion, it can be taken as a positive finding. If no documentation present, a blinded assessor is required to assess this directly

^+^If no preoperative assessment or documentation assume normal at baseline

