##### Secondary outcomes

Binomial outcomes including rehabilitation referrals, pneumonia, PPOI, unplanned ICU admissions, patient-reported complications, and mortality will be analysed using multivariate robust random effects Poisson generalised linear regression.Time-to-event binomial outcomes (e.g. PPC, pneumonia, PPOI, achievement of ambulation goals of 1 and 10 min; and hospital and ICU LOS; and mortality) will be compared by estimating hazard ratios using Cox proportional hazards regression, with and without covariate adjustment where necessary and graphically illustrated using Kaplan-Meier methods.Measures involving estimation of rate of change over time (QOL and functional capacity) will be analysed using repeated-measures mixed effects linear regression or ordered logistic regression for rank-ordered scale measures.Hospital costs will be compared using mixed effects linear regression. Log transformation of highly skewed cost data will be performed. Depending on the adequacy of the data for purposes of economic analysis, a cost-utility may be conducted.

All outcomes will be analysed on an intention-to-treat basis. An intention-to-protocol sensitivity analysis will be performed by identifying as a separate group participants who received more than 80% of planned protocol sessions as per group allocation. Other planned sensitivity analyses will be made according to age (> 65), surgery type (colorectal, upper gastrointestinal, other), preoperative self-reported physical capacity, and gender. Sensitivity of outcome estimates to missing data will be evaluated using multiple imputations. All analyses will be performed using Stata MP2 V14 (StataCorp, College Station, TX, USA).

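### The primary model is called random-effects while centre, the only grouping named, is made fixed; the two statements conflict, and the confidence interval and p value depend on which one the analyst follows

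*Protocol article*

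**What the plan says.** Under Statistical methods, Primary outcome, the absolute and relative PPC rates "will be estimated using multivariate robust random effects Poisson generalised linear regression to allow assessment of binary outcomes". The following sentence states the role of centre: "Treatment centre will be treated as a fixed variable in multi-level models". Under Secondary outcomes, rehabilitation referral, pneumonia, prolonged ileus, unplanned ICU admission, patient-reported complications and mortality "will be analysed using multivariate robust random effects Poisson generalised linear regression".

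The design gives these facts:

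- Outcome measures: "The primary outcome is the first occurrence of a PPC within the first 14 postoperative hospital days". Analysed as a binary result, that is one observation per patient.
- Trial design: "Eligible patients will be randomly assigned via concealed allocation into one of two physiotherapy treatment arms". Individuals are randomised, not groups.
- Trial setting: "The three participating centres represent a range of hospital types in Australia". There are three sites.

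The statistical section names no ward, therapist or other unit that could carry a random effect. It does not say what robust refers to, or at which level a robust variance would be computed.

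**The concern.** A random effect needs a grouping level with more than one observation in each group. Here each patient contributes one binary result, and the only grouping named is centre. If centre is fixed, nothing is left for the random effect to describe. If centre is random, the sentence that makes it fixed is not followed. An analyst therefore has to drop one of the two statements.

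The estimated rate ratio would differ little between the two choices. What is at stake is the standard error, and with it the confidence interval and p value of the confirmatory test. A robust variance adds up score contributions over independent units. With centre fixed and patients as the units, there are up to 288 of them. With centre as the random level, there are three.

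**Working it through.** **1. The plan's own figure.** Inputs from Sample size: 20% against 8%, 1:1 allocation, "with an alpha 0.05 and power 80" per cent. Sidedness is not stated; I take it as two-sided. With the pooled-variance formula and no continuity correction, and p̄ = 0.14:

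n per group = [1.96·√(2·0.14·0.86) + 0.8416·√(0.20·0.80 + 0.08·0.92)]² / 0.12² = (0.9618 + 0.4068)² / 0.0144 ≈ 130.1, so 131 per group and 262 in total.

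This agrees with the article. Nothing in this point changes it.

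**2. Centre fixed, random effect at participant level.** In a Poisson working model a participant-level random effect acts as overdispersion. Binary data are under-dispersed relative to Poisson: p(1−p) is 0.16 against 0.20 at p = 0.20, and 0.0736 against 0.08 at p = 0.08. The random-effect variance should therefore fall to about zero. In 50 simulated trials (n = 288, 20% against 8%), a participant-level gamma-Poisson fit gave a largest estimated overdispersion of 0.0014. Its log rate ratio was within 0.014 of ordinary Poisson. The random effect is redundant, and the model is in effect ordinary Poisson with robust errors.

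**3. Variance taken over three centres.** If the test statistic behaves like t on 2 degrees of freedom but is compared with 1.96:

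P(|t₂| > 1.96) = 1 − 1.96/√(2 + 1.96²) = 1 − 1.96/2.4169 = 0.189.

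**4. Simulation under no effect.** 288 patients, three sites, 1:1 within site, about 3,000 trials per row, log-link Poisson with centre as fixed indicators. Site sizes and site PPC rates are assumptions, because the article gives neither. Rejection at nominal 5%:

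| Site sizes | Site PPC rates | Participant-level robust, 1.96 | Clustered on centre, 1.96 | Clustered on centre, t(2) = 4.30 |
|---|---|---|---|---|
| 96/96/96 | 20/20/20% | 4.6% | 18.9% | 4.9% |
| 144/96/48 | 20/25/15% | 5.3% | 24.4% | 6.2% |
| 192/48/48 | 20/30/15% | 4.4% | 22.2% | 6.1% |

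Further runs with the same site sizes and PPC rates of 14%, 20% or 12/20/28% by site gave similar results. Clustering on three centres rejected in 18-26%. A fitted centre-level gamma random-effects Poisson with robust variance over the three centres rejected in 18-25%. Participant-level robust variance with centre fixed rejected in about 4-6%.

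**5. Power at N = 288, 20% against 8%, equal sites, 2,000 trials.** Participant-level robust: 83.4%. Clustered on centre with t(2): 34.0%. Clustered with 1.96: 79.4%, but at the 18.9% type I error above.

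**6. Where the inflation comes from.** Mean clustered standard error against the empirical standard deviation of the estimate (20% PPC, 1,500 null trials per setting):

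- 96/96/96: 0.213 / 0.245 = 0.87, 13% low.
- 144/96/48: 0.206 / 0.245 = 0.84, 16% low.
- 192/48/48: 0.184 / 0.239 = 0.77, 23% low.

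The standard error is moderately low on average. Since a t(2) critical value alone brings rejection back to about 5-6%, most of the excess comes from using 1.96 with 2 degrees of freedom.

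**The case against.** The strongest reply is that the large error rates belong to a model the article does not specify. The article says centre is fixed and does not mention clustering the variance on it. Keeping centre fixed leads, through step 2, to a robust Poisson model with sound type I error, and the random-effects label then does no harm. This stands. A reader might infer that the primary test as planned has a type I error several times nominal, and the document does not support that. The inflation needs three further choices: centre as the random level against the stated rule, a variance over three clusters, and a normal reference. It would also be too strong to say that the three-cluster standard error is grossly too small on average, or that a participant-level random effect makes the fit fail. The shortfall is 13-23%, and the random effect simply goes to about zero.

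A second reply is that the sentence on centre refers to the repeated-measures models for quality of life and function, which do have a participant level. That is possible. But the sentence stands under Primary outcome, directly after a model that is itself called random-effects.

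A third reply is that the variance estimator, clustering unit and reference distribution are normally left to an analysis plan, and this is a condensed article. That is fair for those details, and their absence is not the point here. The point is that two adjacent statements about the primary model conflict on the page.

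**Conclusion.** The conflict is real. A random-effects Poisson model is named for one binary result per patient, the only named grouping is fixed, and the same model is carried to the binary secondary outcomes. The consequence is conditional:

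- Centre fixed, participant-level robust variance: type I error about 4-6%, power about 83% if all 288 are evaluable.
- Centre as the random level, variance over three clusters, normal reference: type I error about 18-26%.
- The same with t on 2 degrees of freedom: type I error about 5-6%, power about 34% against the planned 80%.

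The figures rest on assumed site sizes and site PPC rates; the 83% and 34% are for equal sites with 20% against 8%. The conflict itself does not depend on those assumptions. It should be settled because it affects the confirmatory test and the choice between readings is unstated.

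**What to change.** Replace the two sentences under Primary outcome with one model: modified Poisson regression (log link) with treatment and centre as fixed effects, participant-level robust (Huber-White) standard errors, no random effect, and no clustering of the variance on centre. Covariate-adjusted versions add the chosen covariates to the same model. Use the same wording for every binary secondary outcome measured once per participant. Keep random effects for the repeated-measures outcomes and name the participant as the level.

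This keeps the stated rule on centre and the evident purpose of the robust Poisson approach for a binary outcome. The cost is a change of wording, made before unblinding. It needs no new data or patients and no change to the sample size.
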